**Fig. 2 Fig2:**
[figure not shown]
Interaction between patient flow and the adaptive trial algorithm

#### Interim analyses {21b}

This is an automated adaptive trial. Our algorithm will review the attendance data every 24 h and perform statistical testing. Two stopping rules will be applied during these daily interim analyses:There is a >95% probability that one arm is best.There is a >95% probability that the difference between the arms remaining in the study is <1%.

If neither of these rules have been satisfied, then the trial (i.e. enrolment) will continue until three months of active screening have elapsed. The Bayesian algorithm will adjust the allocation ratio based on the performance of each arm with respect to the updated posterior probability that each is associated with attendance (Fig. 3).

**Fig. 3 Fig3:**
[figure not shown]
Allocation flow diagram

#### Methods for additional analyses (e.g. subgroup analyses) {20b}

Internal data from a pilot site suggests that around 10% of children who attend the ‘triage and treatment’ clinic will subsequently be identified as having an eye need that requires further specialist ophthalmological assessment in a hospital clinic. These children will be referred from the ‘triage and treatment’ clinic to the local hospital. This subgroup will also receive either the intervention or control reminder messages. Again, the outcome will be attendance on appointed date.

Once the trial is complete, we will perform retrospective subgroup analyses to explore whether attendance within each group was associated with sociodemographic variables. We use multivariable logistic regression to assess whether each sociodemographic variable is associated with attendance. We note that this is an exploratory analysis, providing hypotheses that can be tested in subsequent studies.

We will perform a secondary analysis that excludes participants whose preferred language is neither Setswana nor English.

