Recognising the human, social, and economic drag exerted by cataracts and uncorrected refractive error, many low- and middle-income country (LMIC) governments are ramping up their vision screening programmes. Donor funding is rising in tandem, partly driven by the advent of phone-based screening platforms like Peek Acuity [20, 21] that have made it possible to rapidly screen entire regions with very modest resource requirements.

Screening programmes based on the Peek digital platform are currently operating in seven LMICs. The Botswanan Ministry of Health (MoH) has committed to use Peek software to screen all school children in government schools over 3 years beginning in Summer 2022 [22]. The Peek platform records basic sociodemographic data, visual acuity, referral status, and attendance status for each child. Every time a child is referred a series of three SMS messages are sent to the mobile phone number registered by their parent/guardian (see Table 1). The current SMS message was not developed with reference to behavioural economics principles. According to internal data from Peek screening programmes in other countries and pilot data in Botswana, attendance rates are currently around 50%, i.e. only half of those identified as needing ophthalmic assessment present to services.

We aim to develop two behavioural economics-informed reminder messages; an SMS and a pre-recorded voice message to be used in the new Botswana MoH schools-based vision screening programme, and tested using an embedded, pragmatic, adaptive RCT design.

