**Control: Standard SMS reminder message** **Setswana** Go [name], one wa tlhatlhobiwa matlho mme ga fitlhelwa ona le bothata jwa matlho. Ka jalo, tla ko [location] ka di [date] go tlhatlhobiwa.O kopiwa go tla le karata ya gago ya botsogo. **English** Dear [name], you were examined and found to have an eye problem. Kindly report to [location] on [date] for assessment. Please come with your clinic card. **Intervention: New SMS reminder message** **Setswana** Go motsadi: Re lemogile ngwana wa gago [child’s name] fa ana le bothata jwa matlho. Se, se ka ama tiro ya gagwe ya sekolo. Tswee-tswee, tsisa [child’s name] ko sekolong ka [location and time] o tla tlhatlhobiwa matlho a sa duele Se, se direlwa ngwana mongwe le mongwe mo sekolong yoo nang le bothata jwa matlho Re ka leboga go le bona ka [day and time]. Kea leboga [Leina la ngaka] **English** Dear parent, we have found that your child [child’s name] has an eye problem. This may affect [his / her] schoolwork. Please bring [child’s name] to [location] at [time], [day, date]. We will be doing a free medical check-up for all the children with eye problems in the school. We look forward to seeing [child’s name] on [day and time]. Many thanks, Dr [name], Ministry of Health **Intervention: New voice reminder message** **Setswana** Dumelang: Ke bidiwa ngaka [name], go tswa ko lephateng la botsogo. Ngwana wa gago [leina la ngwna] o tlhatlhobilwe matlho mo bogaufing, mme a fitlhelwa a na le bothata jwa matlho. Fa a ka seka a alafiwa , go ka ama tiro ya gagwe ya sekolo. Setlhopha sa rona sa botsogo, se tlaa bo se le ko sekolong sa ga [leina la ngwana] ka [letsatsi le nako]. Tswee.tswee tsisa ngwana wa gago go tlhatlhobiwa go sena dituelo. Se, se direlwa ngwana mongwe le mongwe yoo nang le bothata jwa matlho. Kea leboga [Leina la ngaka] **English** Hello, my name is Dr [name] from the Ministry of Health. Your child [child’s name] recently had [his/her] eyes checked at school and was found to have an eye problem. If this is not corrected, it could affect their schoolwork. Our medical team will be at [location] on [date/time]. Please bring your child to get a free medical assessment. This is offered to all children with eye problems. We look forward to seeing you and your child on [date/time] Many thanks, Dr [name].	

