### Outcomes {12}

All children who are screened and found to need further assessment and treatment (e.g. refractive services) will be given an appointment, approximately 1 week later, at a specified field ‘triage and treatment’ clinic or at a specialist ophthalmic hospital clinic. The primary outcome is attendance at this pre-specified appointment on the appointment date (yes/no).

The Peek software retains a record of every referred child. When children attend for these appointments, they are checked in using Peek software. This automatically updates their attendance status. Attendance data will be automatically reviewed by an algorithm every 24 h. The great advantage of the Peek-based screening programme is that is a closed data system with complete, unified data records for every person screened, their referral status and their attendance status. No additional data collection activities are required.*Primary outcome*: attendance at clinic on invited date. This is a binary outcome measure (yes/no). We will compare mean outcome rates between arms.*Secondary outcome*: days elapsed between appointment date and attendance. This is because children may miss their appointed day but attend at a later date. We will compare mean number of days elapsed between each arm.*Subgroup analyses*: attendance by age, sex, urban/rural residence, distance to clinic, ethnicity, guardianship, religion, language, household composition, migrant status, parental occupation, housing, assets and income.

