### Sample size {14}

Approximately 1000 children will be screened every day. Based on previous programmes, we expect approximately 160 of these children to be identified as requiring referral for further assessment and treatment. All of these children’s parents/guardians would receive the standard SMS reminders in a standard programme.

The adaptive allocation method that we are using does not use a pre-specified a sample size. Instead, the study will run until one of two criteria is met:There is a >95% probability that one arm is best.There is a >95% probability that the difference between the arms remaining in the study is <1%.

Depending on the effect of the interventions, one of the stopping criteria might be met after a few days; however, it could also take years before reaching a definitive conclusion. We will set a 3-month limit for this current study due to resource constraints.

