### Recruitment {15}

Community sensitisation is being led by the Ministry of Health and Ministry of Education. This includes TV and radio coverage explaining the Pono Yame screening programme. Our field coordinator will visit each region and work with schools to ensure that they are set up to enrol as many children as possible. Every referred child’s data will be included in the primary analysis. Subgroup analyses will only be permitted for children whose parents have consented for their sociodemographic data to be used for research purposes. This is a separate consenting process led by Peek.

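### The exploratory logistic regression of attendance on sociodemographic variables states no allowance for within-school correlation, so standard errors for covariates largely shared within a school may be too small

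*Protocol article*

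**What the plan says.** The protocol article, Methods for additional analyses {20b}, describes a retrospective analysis after the trial: "We use multivariable logistic regression to assess whether each sociodemographic variable is associated with attendance". It adds: "We note that this is an exploratory analysis, providing hypotheses that can be tested in subsequent studies". No significance level is set for it.

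Outcomes {12} lists 14 variables, beginning "attendance by age, sex, urban/rural residence, distance to clinic, ethnicity, guardianship, religion, language" and running on through household composition, migrant status, parental occupation, housing, assets and income.

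The data are grouped by school in several ways:

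- **Screening.** Background and rationale {6a} says the Ministry has committed "to screen all school children in government schools over 3 years".
- **Enrolment.** Under Recruitment {15}, "Our field coordinator will visit each region and work with schools".
- **Call-back.** The new English SMS in Table 1 tells parents: "We will be doing a free medical check-up for all the children with eye problems in the school". The Setswana SMS and voice texts also place the visit at the school.
- **Venue.** Outcomes {12} puts the appointment about a week later at a specified field "triage and treatment’ clinic or at a specialist ophthalmic hospital clinic". Not every appointment is therefore tied to one school.

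The text on statistical methods mentions neither school nor correlation between children.

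**The concern.** Referred children from one school will often share a venue, a date, a screening team and local conditions, and the outcome is attendance on that date. Some correlation of attendance within school is plausible. Ordinary logistic regression computes its standard errors as if children were independent.

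Randomisation by child protects the comparison of arms. It does not protect this regression, because its covariates are not randomised and some cluster by school. For a covariate that is the same for every child in a school, the information depends largely on the number of schools, not the number of children. Distance to clinic and urban/rural residence are the clearest candidates.

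At stake is the reliability of the hypotheses that the analysis is meant to supply. Intervals that are too narrow would make area-level factors look better established than they are.

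**Working it through.** The protocol gives no sample size, alpha or ICC for this regression, so there is no stated figure to reproduce.

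**Inputs from the protocol article**
- Sample size {14}: "Approximately 1000 children will be screened every day", of whom about 160 are expected to be referred. The trial is limited to 3 months.
- Background {6a}: attendance is around 50%.

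**Assumptions, not in the documents**
- Two-sided 5% test.
- ICC of attendance within school: 0.05, range 0.01 to 0.10.
- The 160 daily referrals come from 10, 4 or 2 schools, so m = 160/10 = 16, 160/4 = 40 or 160/2 = 80 referred children per school.
- For the simulation: up to 60 screening days, so 160 × 60 = 9,600 referred children.

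**Step 1: fully school-level covariate.** Design effect DE = 1 + (m − 1) × ICC. True error of a nominal 5% test = 2 × (1 − Φ(1.96/√DE)).

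| ICC | m = 16 | m = 40 | m = 80 |
|---|---|---|---|
| 0.01 | DE 1.15, 6.8% | DE 1.39, 9.6% | DE 1.79, 14.3% |
| 0.05 | DE 1.75, 13.8% | DE 2.95, 25.4% | DE 4.95, 37.8% |
| 0.10 | DE 2.50, 21.5% | DE 4.90, 37.6% | DE 8.90, 51.1% |

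Example: ICC 0.05 and m = 40 give DE = 1 + 39 × 0.05 = 2.95, and 1.96/√2.95 = 1.14, so the error is 25.4%.

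The same result can be put without a significance threshold. The plain interval is 1/√DE of its proper width: at ICC 0.05, 1/√1.75 = 76%, 1/√2.95 = 58% and 1/√4.95 = 45%.

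School size matters as much as the ICC. At ICC 0.05 the error is 7.4% with 5 children per school, and 51.2% with one school per screening day (m = 160). At ICC 0 it is 5% throughout.

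**Step 2: covariate only partly shared within school.** DE = 1 + (m − 1) × ICC of attendance × ICC of the covariate. With attendance ICC 0.05:

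| Covariate ICC | m = 16 | m = 40 | m = 80 |
|---|---|---|---|
| 0.5 | 9.5% | 16.3% | 25.6% |
| 0.8 | 12.1% | 22.1% | 33.7% |

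**Step 3: model fitted within each arm.** The section speaks of attendance within each group. If that means trial arm, 40 children per school split evenly over 2 or 4 arms leaves 20 or 10 per school. At ICC 0.05 this gives DE = 1 + 19 × 0.05 = 1.95 (16.0%) or 1 + 9 × 0.05 = 1.45 (10.4%), instead of 25.4%.

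**Step 4: simulation check.** Beta-binomial attendance with mean 0.5, 9,600 children, 600 runs per setting. The school-level covariate was null and constant within school.

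| ICC, m | Plain logistic | School-clustered standard errors |
|---|---|---|
| 0.01, 40 | 10.8% | 6.8% |
| 0.05, 40 | 24.2% | 3.8% |
| 0.10, 40 | 36.3% | 5.2% |
| 0.05, 80 | 36.5% | 4.7% |
| 0.10, 80 | 52.0% | 4.3% |

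The simulation agrees with the formula, and clustering restores roughly the nominal level. In the same runs a child-level covariate that varied independently within school stayed between 3.5% and 5.2% under the plain model.

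**The case against.** The strongest reply is that the section names only a model family. A logistic regression with school-clustered standard errors would fit the sentence, and such detail is commonly left to an analysis plan, which is not shown. This stands in part. A reader might infer that the plan treats children as independent, but the documents do not say so. What remains is that the protocol names a method which, run as written, makes no allowance for the grouping that the protocol itself describes. A better method is available at almost no cost.

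Other stronger readings also go further than the documents allow:

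- **That area-level factors will look significant far too often.** This depends on an ICC and a school size that the documents do not give. At ICC 0.01 with 5 to 20 children per school the error is only 5.5% to 7.2%. Adjusting jointly for distance, residence, language and housing would also absorb some between-school variation, and Recruitment {15} restricts these analyses to consenting families, which makes clusters smaller.
- **That many null factors would be declared associated.** Of the 14 listed variables, two are plausibly close to school-level, and even those are not stated to be constant within a school. Preferred language, ethnicity, housing and assets are collected child by child, and nothing shows that they are nearly constant within a school.
- **That later messages would be tailored from this output.** The Discussion says that the trial approach could be used to test messages varied by recipient demographics. It does not link that to this regression.
- **That the trial's main result is at risk.** This point does not touch the primary comparison or the stopping rules, since children are randomised individually.

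The exploratory label and the absence of an alpha lower the stakes. They do not make a standard error valid, because an interval of the wrong width misleads in an exploratory analysis too.

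**Conclusion.** The point holds as a minor one. The named regression has no stated allowance for children being screened, and largely called back, by school. If attendance correlates within school, standard errors will be too small for covariates largely shared within a school, chiefly distance to clinic and urban/rural residence.

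Under the assumed ranges, a nominal 5% test of a fully school-level covariate has a true error of about 7% to 51%, and 14% to 38% at ICC 0.05. For a given ICC and school size these are upper bounds. They are lower for partly shared covariates or within-arm models, and variables that vary independently within school, such as sex, are little affected. The direction (intervals too narrow) follows from any positive within-school correlation of attendance and covariate; the size rests on assumptions.

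**What to change.** In Methods for additional analyses {20b}, state that the logistic regression will use cluster-robust standard errors with school as the cluster, or GEE with an independence working correlation. If school is not in the exported data, cluster by clinic location and appointment date, which the reminder messages in Table 1 already use. Report the number of schools alongside the number of children.

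The cost is one sentence and one software option. The small downside is wider intervals for school-level variables. If within-school correlation proves negligible, the results will barely change.

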#### Methods in analysis to handle protocol non-adherence and any statistical methods to handle missing data {20c}

The primary analysis only requires trial arm and the outcome (attendance) to be recorded. The trial arm should be recorded automatically as part of the Peek coding, and if it was missing it would be due to a bug in the coding. If this occurred, there is no statistical method that could be used to recover that data so any records with trial arm missing would not be included in the updating of the probability that an arm is best. We will check the code every 24 h to ensure that it is running as expected and correct any errors that we find immediately. The outcome cannot be missing, as a participant is set as ‘not attended’ until the point where they are updated as having ‘attended’.

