### Assignment of interventions: blinding

#### Who will be blinded {17a}

Trial participants will not be blinded. Programme implementers will check in participants when they attend clinic using Peek Capture. The software will automatically record the date and the time elapsed since referral. The adaptive algorithm will analyse attendance rates between arms according to pre-defined rules. Screening programme staff and data analysts will be blinded to assignment status. A small team of unblinded human statisticians will monitor the algorithm’s performance. They will double-check the algorithm’s working every 24 h during the trial and will repeat the final analysis comparing each arm. They will have the power to stop the trial, but they will not influence allocation.

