### Data collection and management

#### Plans for assessment and collection of outcomes {18a}

Referral status, attendance status and days elapsed since referral will be collected using the Peek Capture system on Android devices. Every time a participant is referred and every time they attend at clinic, they are checked in using an android device operating Peek Capture software. Additional data on sociodemographic characteristics will be collected when participants initially present to the screening programme.

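### The primary outcome is attendance on the appointment date, but the stated data rule is an open-ended status with no date limit, and the article does not say which of the two the algorithm reads

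*Protocol article*

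**What the plan says.** Outcomes {12} ties the endpoint to a day: "The primary outcome is attendance at this pre-specified appointment on the appointment date (yes/no". The sections on retention {18b} and on additional analyses {20b} use the same on-the-day definition.

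Outcomes {12} also describes how the record changes. A child who comes to clinic is checked in, and "This automatically updates their attendance status". The algorithm works from these records: "Attendance data will be automatically reviewed by an algorithm every 24 h". The section adds a secondary outcome on delay and gives the reason: "This is because children may miss their appointed day but attend at a later date".

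The missing-data section {20c} then says what the primary analysis uses: "The primary analysis only requires trial arm and the outcome (attendance) to be recorded". It links this to the daily updating of the probability that an arm is best, and states the rule for the outcome: "The outcome cannot be missing, as a participant is set as ‘not attended’ until the point where they are updated as having ‘attended".

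On data items, {18a} says "Referral status, attendance status and days elapsed since referral will be collected using the Peek Capture system on Android devices", and the blinding section {17a} says "The software will automatically record the date and the time elapsed since referral".

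**The concern.** Take a child who misses the appointment and is checked in nine days later. Under {12} that child is a failure. Under {20c}, read literally, the child is a failure for nine days and then a success. An on-the-day outcome becomes final when the day ends, whereas a status that stays open until some check-in changes it measures whether the child has attended at all so far.

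The difference matters more here than in a fixed design, because this variable drives daily allocation and both stopping rules without human input. A later analysis plan can redefine the reported endpoint but cannot undo allocation or stopping already based on another one.

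Two consequences follow if the undated status is what the algorithm reads. First, from the first day, the trial adapts on ever-attendance while reporting on-date attendance, and the two could rank messages differently. Second, the status has no fixed window. Arms 3 and 4 enter about six weeks after arms 1 and 2, so the SMS-only arms would have had more time to turn late attenders into successes, even if all four messages worked equally well.

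**Working it through.** **Step 1. The sections side by side.**

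| Child | Outcomes {12} | Rule in {20c}, read literally |
|---|---|---|
| Checked in on the appointment date | 1 | 1 |
| Checked in only after that date | 0 | 0, then 1 |
| Never checked in | 0 | 0 |

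The rules differ only for late attenders, whom {12} expects.

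**Step 2. Inputs for the size.** From the article: voice arms enter after 6 weeks; the appointment is about 1 week after referral; the limit is three months (about 13 weeks). Assumed, because the article gives no figure: a share *L* of referred children attends late (5%, 10%, 20%), with exponential delay of mean *m* = 2 or 4 weeks. Also assumed: all arms truly identical, steady enrolment, 1:1 allocation to week 6 and equal over four arms afterwards, and only children whose appointment date has passed are counted.

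**Step 3. Formula.** By time *u* after the appointment, a fraction *L*(1 − e^(−u/m)) of children has become a late success. At week *W*, children referred up to *T* = *W* − 1 have passed their date. Let F(t) = t − m(1 − e^(−t/m)), the integral of 1 − e^(−u/m) from 0 to t.

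- Voice arm: V = F(T−6)/(T−6)
- SMS-only arm: S = [0.5(F(T) − F(T−6)) + 0.25 F(T−6)] / [0.5×6 + 0.25(T−6)]
- False lead = L(S − V)

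**Step 4. Week 8, m = 2.** T = 7, F(7) = 5.060, F(1) = 0.213. S = [0.5(5.060 − 0.213) + 0.25×0.213]/3.25 = 0.762 and V = 0.213. With L = 10% the false lead is 0.10 × 0.549 = 5.5 points.

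| Week | m (weeks) | S | V | L = 5% | L = 10% | L = 20% |
|---|---|---|---|---|---|---|
| 8 | 2 | 0.762 | 0.213 | 2.7 | 5.5 | 11.0 |
| 8 | 4 | 0.560 | 0.115 | 2.2 | 4.4 | 8.9 |
| 9 | 2 | 0.810 | 0.368 | 2.2 | 4.4 | 8.8 |
| 9 | 4 | 0.618 | 0.213 | 2.0 | 4.1 | 8.1 |
| 13 | 2 | 0.884 | 0.683 | 1.0 | 2.0 | 4.0 |
| 13 | 4 | 0.750 | 0.482 | 1.3 | 2.7 | 5.4 |

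The last three columns are points of attendance. Under the on-date definition every entry is zero. The article's second stopping rule uses a margin of 1%.

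**Step 5. Effect on the algorithm's probabilities.** The prior was first checked against the article's own figure: Beta(100,100) has a 90% interval of 0.442–0.558, matching the stated 0.44–0.56, so the prior was read that way. Inputs: 160 referrals per working day, 50% on-date attendance in every arm, a 5-working-day lag to appointment, mean delay of 10 working days, equal allocation after voice entry. Ten working days after voice entry:

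| Late share | SMS-only rate | Voice rate | P(an SMS-only arm is best) |
|---|---|---|---|
| On-date outcome | 0.500 | 0.500 | 0.35 |
| 5% | 0.538 | 0.509 | 0.84 |
| 10% | 0.575 | 0.517 | 0.99 |
| 20% | 0.650 | 0.535 | >0.99 |

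The 0.35 is below one half because the newer arms have wider posteriors.

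**Step 6. Effect on stopping.** In 150 simulated trials per scenario, with allocation following these probabilities and the first stopping rule applied only after voice entry, the trial stopped wrongly for one SMS-only arm in 0.7%, 4% and 83% of runs at 5%, 10% and 20% late. With the on-date outcome it stopped for an SMS-only arm in 0% of runs and for a voice arm in 3.3%. The undated status lifts both SMS-only arms alike, so at the lower shares neither easily passes 95% alone.

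**The case against.** The strongest reply is that the endpoint is defined the same way throughout and that {20c} only explains why no outcome can be missing. On that reading, attendance in {20c} means the outcome already defined, which defaults to no unless a check-in meets the definition. The date test would be a derivation detail that belongs in the full protocol, the code or the figures, which are not shown.

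Part of this stands. A reader might infer that the algorithm does adapt and stop on a different endpoint. The article does not say so: no section states that late check-ins are counted, and none states that they are excluded. A reader might also infer from {18a} that on-date attendance cannot be recovered, because days since referral do not fix the appointment day. That is not supported either. The blinding section says the software records the date, the message templates carry the appointment date, and the secondary outcome needs both. Finally, a reader might infer a general advantage for older arms. Arms 1 and 2 start together, so the unequal collection time cannot separate them. It arises only after the voice arms enter, with data pooled over time.

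What the reply does not remove is that {20c} is more than silent. It states a rule for the variable used in the primary analysis and the probability update, with an open end and no date among the fields it needs. Followed as written, that rule conflicts with {12}.

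**Conclusion.** The concern holds as a conflict between two stated rules, with the version used by the algorithm left open. If the undated status is used, allocation and stopping follow ever-attendance instead of the stated endpoint. After voice entry, identical arms would then show a false lead for the SMS-only arms of about 2–11 points at week 8 and 1–5 points at week 13.

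These figures rest on an assumed late share of 5–20%, an assumed mean delay of 2–4 weeks, and equal allocation after week 6, whereas the article allocates in proportion to the probability of being best. At 5–10% late, the expected harm falls mainly on allocation and estimates; frequent wrong stops appear only at 20%. The conflict should be settled before recruitment, because the variable controls the trial as it runs and the correction is nearly free.

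**What to change.** State in Outcomes {12}, Statistical methods {20a} and the missing-data section {20c} that the algorithm and the final analysis use one outcome: 1 if the check-in date equals the child's appointment date, 0 if that date has passed without a check-in on it. It is scored only once the date has passed and is never changed by a later check-in. This also stops children whose appointment is still ahead from being counted as failures, a separate effect of the same sentence that is not included in the figures here.

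Use late check-in dates only for the secondary outcome, counted from the appointment date, and add the appointment date to the data items in {18a}.

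Both dates are already available to the programme and, by the trial status given, recruitment has not begun. The cost is a line of code and a few sentences. The small downside is that observed attendance will be lower than the undated status would show.

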### Assignment of interventions: allocation

#### Sequence generation, concealment and implementation {16a, 16b, 16c}

Participants will initially be randomly allocated into two arms using computer-generated blocks of 12. As allocation and intervention delivery (sending SMS messages) is fully automated, there is no need for any of the human investigators to know participant allocation status. Once the first participants attend refractive services, the algorithm will begin adjusting the allocation ratio to favour the best-performing arms. There is no need for the investigators to see allocation status at this stage either. The data safety monitoring committee will be fully unmasked to allocation status and all outcome data and will have the power to stop the trial or suspend any arm.

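### As written, {20c} counts children whose appointment is not yet due as non-attenders in the daily update, so allocation can oscillate and the best-arm rule can fire on an artefact

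*Protocol article*

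**What the plan says.** All references are to the protocol article.

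- **Outcomes {12}.** Referred children "will be given an appointment, approximately 1 week later". The primary outcome is binary attendance on that date. "Attendance data will be automatically reviewed by an algorithm every 24 h".
- **Missing data {20c}.** "The outcome cannot be missing, as a participant is set as ‘not attended’ until the point where they are updated as having ‘attended". The one exclusion named concerns a coding fault: "any records with trial arm missing would not be included in the updating of the probability that an arm is best".
- **Allocation {16a–c}.** Two arms start in blocks of 12, and then: "Once the first participants attend refractive services, the algorithm will begin adjusting the allocation ratio to favour the best-performing arms".
- **Statistical methods {20a} and interim analyses {21b}.** Each day the posterior probability that each arm is best is recomputed, the next day's allocation is made proportional to it, and two stopping rules are applied. Rule 1 is a probability above 95% that one arm is best. Rule 2 is a probability above 95% that the remaining arms differ by less than 1%.
- **Intervention description {11a}.** Two voice-message arms are planned to join after 6 weeks.

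**The concern.** The outcome is undetermined for about a week after allocation, yet {20c} gives it a value from the moment of referral and denies that it can be missing. No 'pending' state exists in the text. Once the trial is running, roughly a week of newly allocated children is always waiting, and each counts against the arm that received them.

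Under fixed equal allocation this would nearly cancel between arms. Under this design it does not, because the arm that looks better is given more children and so holds more provisional failures. The probability of being best, the next day's allocation and both stopping rules then reflect how recently each arm was used as well as how well its message works. At stake are which message is named best in a national programme and the stated aim of observing how the algorithm handles arms added part-way.

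**Working it through.** **The plan's own figure.** The prior is printed as Beta(100,000), with a 90% credible interval of 0.44–0.56. Beta(100,100) gives 0.442–0.558, which agrees, so it is used here.

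**Inputs from the document.** {14}: "we expect approximately 160 of these children to be identified as requiring referral" daily. {6a}: "attendance rates are currently around 50" per cent. From {16a–c}, {20a} and {21b}: 1:1 until first outcomes, then allocation proportional to the probability of being best, with daily looks.

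**Assumptions.** Lag of 5 to 7 daily updates for about one week; 60 to 65 updates for three months; constant referrals.

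**Mechanism.** Take an arm with true rate p, m matured children and w pending children. If pending children count as failures, its posterior mean is

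(100 + p·m) / (200 + m + w),

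which falls as w rises. Suppose two identical arms at p = 0.5, with m = 560 each and 7 × 160 = 1,120 pending.

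- Pending excluded: 380/760 = 0.500 in both arms.
- Pending split 50:50 (560 each): 380/1,320 = 0.288 in both arms. The distortion cancels.
- Pending split 60:40 (672 and 448): 380/1,432 = 0.265 against 380/1,208 = 0.315. The posterior SDs are about 0.0117 and 0.0134, so z = 0.049/0.0177 ≈ 2.8. The probability that the arm with more pending children is best is about 0.003, and rule 1 would stop the trial and name a winner between identical messages.

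**Simulation of the whole two-arm trial.** Ranges span separately programmed runs. With 4,000 runs per setting, the Monte Carlo SE of a 17% result is √(0.17 × 0.83/4,000) ≈ 0.6 points.

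| Quantity | Pending counted as failure | Matured outcomes only |
|---|---|---|
| Identical messages: rule 1 fires | essentially 100% (median day 13–14 at lag 5, 21 at lag 7) | about 36–38% |
| 50% v 55%: inferior arm declared best | 23–26% (lag 5), 17–19% (lag 7) | about 0.1–0.2% |
| 50% v 60%: inferior arm declared best | about 4–9% | 0% |
| Identical messages, no stopping: crossings of 50:50 in 60 updates | 35–42 | 4.6 |

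Sensitivity: extending to 90 updates at lag 7 gives essentially 100% against 41% null firing. {20a} speaks of about 1,000 children enrolling daily. At that rate the 50% v 55% error is 31–53% against 0%.

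**Check that adaptation is the cause.** Under fixed 1:1 allocation, counting pending children as failures raises null firing only from 38% to 50%, and the wrong-arm rate at 50% v 55% only from 0.1% to 0.2%.

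**Arms added at week 6.** Take day 30, lag 7, identical messages and equal-sized old arms, with 30 × 160 = 4,800 children allocated and 1,120 of them pending.

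- On opening, each old arm sits at (100 + 920)/(200 + 2,400) = 0.392, while a new arm sits at its prior mean of 0.500. The new arms take nearly everything.
- One day later each new arm has about 80 children, all pending: 100/280 = 0.357. Each old arm has risen to (100 + 960)/2,600 = 0.408. Allocation reverses.

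Run without stopping, the simulated new-arm share goes from about 100% to 7% or less the next day, then about 1%, and returns to about 100% eight days after opening. With both voice arms truly 10 points better (lag 5, no stopping), they receive about 1,920–1,930 children in total, against about 5,230 with matured outcomes.

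**The case against.** The strongest reply is that this is a literal reading of a sentence about missing data. {20c} may describe only the default status in the record, and the missing-arm rule deals with a coding bug and need not be an exhaustive list of exclusions. {12} defines the outcome on the appointment date, which fits a date filter, and {16a–c} shows awareness that outcomes arrive late. Figures 2 and 3, which concern patient flow and allocation, are not shown, nor is the code. This stands as a limit: the documents do not prove that the running algorithm behaves this way. It does not rescue the text, which leaves no room for a pending outcome. The start rule in {16a–c} only delays adaptation and does not remove children who are pending later.

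Human oversight is the second reply. Unblinded statisticians check the algorithm every 24 h and repeat the final analysis, and the monitoring committee can suspend an arm. Such swings might well be noticed, but a check against the stated rule would find the rule correctly applied.

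Three stronger readings are tempting but not supported.

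- *New arms are shut off for good.* They swing back once their first children mature; the result is oscillation and under-allocation. The week-6 results also require the trial still to be running (rule 1 not applied earlier) and the new arms to enter at the probability-proportional share, which the document does not specify.
- *Every false stop comes from this rule.* About 36–38% null firing remains with matured outcomes. It comes from daily looks at 95%, a separate issue.
- *The inferior message wins in over a third of trials at a 5-point gain and 160 referrals a day.* That needs a lag of about 2 days (37%), which does not match an appointment about a week away.

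**Conclusion.** The concern holds for the rule as written. Read literally, {20c} enters children who are not yet due as failures, and adaptive allocation turns that into a distortion that differs between arms. With identical messages, rule 1 fires in essentially every trial against about 36–38% with matured outcomes. With a true 5-point gain, the inferior message is declared best in about 17–26% of trials against about 0.1–0.2%; with 10 points, in about 4–9%. These figures rest on the stated assumptions: 160 referrals a day, 50% attendance, Beta(100,100), 1:1 until first outcomes and a lag of 5–7 updates. Whether the deployed code does this cannot be settled from the article. Either the algorithm or its description needs correcting before enrolment.

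**What to change.** In {20c}, and in the algorithm if it does not already do so, state that a child enters the daily update and both stopping rules only once the appointment date has passed and that day's check-ins have synced. Until then the outcome is 'pending', kept distinct from 'not attended', and excluded. State that the final comparison of arms follows the same rule. If Figures 2 and 3 or the code already filter by date, only the wording of {20c} needs to change.

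The cost is one date filter and one or two sentences. The downside is that adaptation reacts about a week later, a delay that the appointment interval imposes in any case. This change does not address the false stops that remain from daily looks at 95%.
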